### Study design and participants: inclusion, exclusion and drop out criteria

2.1

We planned an observational double arm non-randomized study in two centers to compare the safety and efficacy of either mirabegron (50 mg/day) or solifenacin (5 mg/day) in OAB patients. The protocol provides that ophthalmologists will be blinded regarding which patients have been treated with both drugs. We planned to enroll 312 subjects aged between 50 and 80 years with a diagnosis of early or moderate dry AMD, according to ARDS classification, and OAB. The patients will be enrolled at the Department of Ophthalmology of the University of Lublin, Poland and the University of Naples Federico II, Italy from December 2025 to October 2026. All patients will be followed for a 12-month period. The study will be conducted in compliance with the tenets of the Declaration of Helsinki, accepted by the local Ethics Committee, protocol numbers 2025a45673 at the University of Naples Federico II, Italy and KE-0379/97/2025 at the University of Lublin, Poland.

All study participants will provide written informed consent prior to enrollment and for the use of their clinical data for scientific research in an anonymized manner. Inclusion and exclusion criteria are summarized in Table 1.

**Table 1 tab1:** Inclusion and exclusion criteria.

Inclusion criteria
Age 50–80-year-old
Patients with early or moderate dry AMD in one or both eyes
Patients with wet AMD in the other eye
OAB treated for at least 6 months with either mirabegron or solifenacin
BCVA > 65 EDTRS letters
Exclusion criteria
Any contraindication to β-agonists or anticholinergics
Allergy to β-agonists or anticholinergics
Uncontrolled hypertension; tachycardia; atrial fibrillation; long QT or concomitant treatment with drugs that cause lengthening of the QT interval
Patients exposed to experimental drugs other than mirabegron or solifenacin, complement factor inhibitors, photobiomodulation therapy, transscleral lutein iontophoresis therapy or recent surgery (e.g., 3 months)
Recurrent urinary infections
Renal or hepatic failure
Signs of ocular inflammation
Any other ophthalmic diseases such as dry eye, glaucoma, acute or chronic uveitis, advanced cataract
Pregnancy

AMD, age-related macular degeneration; OAB, overactive bladder; BCVA, best corrected visual acuity; EDTRS, early treatment diabetic retinopathy study; QT interval, the time from the start of the Q wave to the end of the T wave in an electrocardiogram.

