The unit of analysis will be the eye. When both eyes meet eligibility criteria, both eyes will be included. The study will stop if severe hypertension, tachycardia, or atrial fibrillation develops; in this case, the opportunity to reduce the dose of mirabegron may be considered. The patient will have the right to withdraw their consent at any point during the study. Mirabegron displays no significant increase in major adverse cardiovascular events with a cardiovascular profile almost comparable to that of antimuscarinic agents. In our study, the safe profile of a 50 mg dosage will be associated with an increase of approximately 1 bpm for heart rate and 0.4–0.6 mmHg for systolic/diastolic blood pressure.

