Assuming a 12% progression rate in the solifenacin group and a 3% progression rate in the mirabegron group at 12 months (absolute difference 9%), with *α* = 0.05 (two-sided) and power = 80%, the required sample size is n ≈ 134 participants per group (net, without accounting for dropouts), computed using the standard formula for comparison of two proportions. The choice of the absolute difference of 9% is not based on clinical data as no clinical trials using either solifenacin or mirabegron to verify the rate of dry AMD progression to the wet form have been performed. This absolute difference was selected as a clinically meaningful planning effect size (Number Needed to Treat ≈ 11 over 12 months). Because eligibility and outcomes are defined at the eye level and participants may contribute with one or two eligible eyes, this calculation should be considered a planning approximation; all inferential analyses will account for within-participant correlation using robust standard errors clustered by participants.

To allow for an expected 15% dropout/non-compliance rate, the enrollment target was increased accordingly, yielding n ≈ 157 participants per group (314 total). For reporting and logistical reasons this has been pragmatically rounded to 156 participants per group (312 total); the protocol will state that this figure includes an allowance for approximately 15% attrition.

The sample size was computed according to the classical formula for two independent proportions:

$$n=\frac{\left(Z_{1-\frac{\alpha }{2}}\sqrt{2p(1-p)}+Z_{1-\beta }\sqrt{p_{1}(1-p_{1})+p_{2}{\left(1-p_{2}\right)}^{2}}\right)}{{\left(p_{1}-p_{2}\right)}^{2}}$$

Where *p*_1_ = 0.12, *p*_2_ = 0.03, *p* = (*p*_1_ + *p*_2_)/2, *α* = 0.05, and 1-*β* = 0.80. The resulting net sample size is approximately n ≈ 134 per group; after adjusting for ~15% attrition the enrollment target is *n* ≈ 157per group (rounded for the protocol to 156 per group).

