All statistical analyses will be done using Python in the Google Colab cloud computing environment and/or SPSS (version 31). The primary confirmatory timepoint will be 12 months. To control type 1 error across the pre-specified primary endpoints, *p*-values will be adjusted using the Holm procedure (two-sided). Statistical significance will be set at a two-sided α = 0.05. Analyses will be conducted using exposure-defined (as-treated) and protocol-adherent approaches, rather than randomized intention-to-treat terminology. Continuous variables will be summarized as mean ± standard deviation or median with interquartile range, depending on the data distribution assessed by the Shapiro–Wilk test. Categorical variables will be presented as frequencies and percentages. Baseline characteristics will be described and group balance will be assessed using standardized differences, rather than relying on significance testing of baseline differences.

The primary outcome measures include conversion to wet AMD at 12 months, and outer retinal morphology parameters obtained from SD-OCT and FAF, including RPD type, ONL thickness, ChT, CMT, and FAF changes. These will be analyzed using mixed-effects models to account for repeated measures at T0, 6 months, and 12 months, with fixed effects including treatment group, time, and treatment×time interaction. Robust standard errors clustered by participants will be used to account for correlation between eyes from the same participant. Adjustments will be made for baseline BCVA, age, sex, AMD stage, contralateral wet AMD status (yes/no), and other relevant factors. If assumptions of normality are not met, appropriate non-parametric methods or robust modeling approaches will be used.

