Secondary outcomes will consist of changes in BCVA (ETDRS letters) and mean MS (microperimetry). These will be analyzed using the same modeling method, with post-hoc pairwise comparisons adjusted for multiple testing using the Bonferroni method. Given the non-randomized design, primary analyses will use a pre-specified adjusted model including key baseline prognostic factors (age, sex, baseline BCVA, AMD stage/severity, comorbidities, baseline symptom severity, and contralateral wet AMD status), and results will be reported as effect estimates with 95% confidence intervals. Safety parameters (heart rate, blood pressure, oxygen saturation, need for respiratory support) will be reported as the number and percentage of patients with pathological values, without correlation to other variables. Adverse event rates will be compared using χ^2^ or Fisher’s exact tests.

Extreme values will be checked for plausibility and kept unless classified as data entry mistakes or physiologically unlikely. Missing data will be managed according to their missingness pattern, and sensitivity analyses will be conducted to assess the reliability of the results. Exploratory subgroup analyses will be performed according to AMD stage (early vs. moderate). Sensitivity analyses will exclude participants who stop taking mirabegron before 6 months or require a dose adjustment. In Figure 1, trial flow is schematically represented.

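### The sensitivity analysis removes early stoppers from the mirabegron group only, so selection alone can create or hide a group difference and the analysis cannot serve as a robustness check

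*Protocol article*

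**What the plan says.** The study is an "observational double arm non-randomized study in two centers" (section 2.1), so the comparison rests on adjustment for baseline factors. The rule at issue stands near the end of section 2.3: "Sensitivity analyses will exclude participants who stop taking mirabegron before 6 months or require a dose adjustment". Nothing in the article applies a corresponding exclusion to solifenacin.

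Three other statements bear on how to read it:

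- Section 2.1 states: "The study will stop if severe hypertension, tachycardia, or atrial fibrillation develops". It continues that in this case "the opportunity to reduce the dose of mirabegron may be considered". This is the only dose change the article mentions, and it is tied to cardiovascular events.
- Table 1 requires at entry: "OAB treated for at least 6 months with either mirabegron or solifenacin".
- Section 2.3 describes the main approach: "Analyses will be conducted using exposure-defined (as-treated) and protocol-adherent approaches, rather than randomized intention-to-treat terminology". It does not define these terms further.

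**The concern.** A sensitivity analysis should vary one assumption and leave the comparison otherwise fair. This one changes the make-up of one group only, and does so using events after baseline. Mirabegron users who stop or change dose leave the analysis, while solifenacin users who stop early stay in. What remains is a persistent, tolerant mirabegron subset against all solifenacin users.

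The excluded participants are unlikely to be a random subset, since the article links mirabegron dose reduction to cardiovascular events. Adjustment for baseline covariates cannot be relied on to undo selection that happens later.

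What is at stake is interpretation. If this analysis agrees with the main result, the agreement may come from selection. If it disagrees, the disagreement may too. Either way the reader learns little about robustness.

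**Working it through.** **Inputs from the article (section 2.3).** "Assuming a 12% progression rate in the solifenacin group and a 3% progression rate in the mirabegron group at 12 months"; two-sided alpha 0.05; power 80%; 134 per group net; 15% dropout or non-compliance, not split by group; 156 per group enrolled.

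**The plan's own figure.** With p1 = 0.12, p2 = 0.03 and mean p = 0.075, the standard pooled formula (square on the whole numerator) gives

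n = [1.960·√(2·0.075·0.925) + 0.842·√(0.12·0.88 + 0.03·0.97)]² / 0.09² = (0.730 + 0.309)² / 0.0081 ≈ 133.3, so 134 per group.

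This reproduces the stated 134. Then 134/0.85 = 157.6, against the stated 157, rounded to 156.

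**Selection with no drug effect.** Let both groups truly convert at 12%. Let a share s of mirabegron users be excluded, with RR times the conversion risk of those kept. Then

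kept rate = 0.12 / (1 − s + s·RR),

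while solifenacin stays at 12%. Both s and RR are assumptions; the documents give neither.

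| s | RR | Kept mirabegron rate | Spurious difference |
|---|---|---|---|
| 5% | 2 | 0.12/1.05 = 11.4% | benefit 0.6 points |
| 10% | 2 | 0.12/1.10 = 10.9% | benefit 1.1 points |
| 15% | 2 | 0.12/1.15 = 10.4% | benefit 1.6 points |
| any | 1 | 12.0% | none |
| 5% | 0.5 | 0.12/0.975 = 12.3% | harm 0.3 points |
| 15% | 0.5 | 0.12/0.925 = 13.0% | harm 1.0 point |
| 15% | 3 (outer case) | 0.12/1.30 = 9.2% | benefit 2.8 points |

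**Effect on a test.** For an unadjusted two-proportion test of 156 solifenacin against 132.6 mirabegron participants (156 × 0.85), the two-sided rejection rate under no effect is 6.9% at s = 15%, RR = 2, and 11.5% at s = 15%, RR = 3, instead of 5%.

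**Same rule in both groups.** If the stopping pattern is also the same in both, the two kept rates are equal and the expected difference is 0. If patterns differ, some selection remains. For example, with RR = 2, 15% excluded from mirabegron and 5% from solifenacin leave 10.4% against 11.4%, a difference of 1.0 point instead of 1.6.

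**Power for 12% against 3%**, from Φ[(0.09 − 1.96·SE0)/SE1] with SE0 pooled and SE1 unpooled:

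- 15% excluded from both groups (132.6 each): SE0 = 0.0323, SE1 = 0.0319, power 79.8%.
- 15% excluded from mirabegron only (156 and 132.6): SE0 = 0.0318, SE1 = 0.0299, power 82.2%.

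These calculations count participants, as the plan's own sample size does, and ignore covariate adjustment and clustering of eyes.

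**The case against.** The strongest reply is that this sentence governs a supporting analysis only. The pre-specified adjusted model, the 12-month confirmatory timepoint and the Holm adjustment do not depend on it. That stands, and it limits the severity.

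The reply on size also largely stands. The plan's 15% combines dropout with non-compliance and is not a mirabegron stopping rate. Participants lost to follow-up have no 12-month outcome in any analysis. People enter after at least six months on treatment, so many who tolerate the drug badly may already have left. Nothing in the article says that stopping mirabegron goes with a higher or lower risk of wet AMD. Even the 1.6-point case is only about 0.4 standard errors (SE about 3.7 points at 156 against 133). What survives is that the possible error is one-directional by construction once the excluded differ in risk, and that it is easily avoided.

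It is also fair to say that the dose criterion does not expressly name a drug. Reading it as mirabegron-only follows from the sentence and from section 2.1. The stopping criterion needs no such inference.

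A reader might go further and infer that no planned analysis keeps every eligible eye in the group of the drug taken at baseline, or that the set carrying the Holm-adjusted test is left open. The article does not support a finding there. Its term for exposure may well mean the drug at entry, since participants arrive already on one of the two drugs, and defining analysis sets is commonly left to a full protocol or SAP that is not shown.

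**Conclusion.** The point holds for this one sensitivity analysis. As written, it selects on post-baseline behaviour in the mirabegron group alone, so its result cannot be taken as evidence that the main finding is robust.

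It would be too strong to say that the rule must produce a difference or that it favours mirabegron. There is no bias if those excluded have the same conversion risk as those kept, and the sign can go either way. Under the assumed range of 5–15% excluded, the distortion runs from a 1.0-point spurious harm (half the risk) to a 1.6-point spurious benefit (twice the risk), against a planned effect of 9 points. These figures illustrate the mechanism; they do not estimate the bias in this study. The primary analysis is untouched, and the severity is moderate.

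**What to change.** Reword the sentence so that the same discontinuation or dose-change criterion applies to participants on either drug, over the same follow-up window. State that the six months are counted from T0. Counted from the start of treatment, the stopping criterion could exclude nobody, because entry already requires at least six months on the drug. Report the number excluded in each group and for which reason, so that readers can see whether the stopping patterns differ; a common rule does not remove selection if they do.

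This is a change to the wording of one analysis, plus recording stopping and dose changes in the solifenacin group as in the mirabegron group. The statistical cost is about 2 points of power in this sensitivity analysis (79.8% instead of 82.2% if 15% are excluded). The change concerns who is analysed and proposes no dose or clinical rule.

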**Figure 1 fig1:**
[figure not shown]
Schematic flow of the proposed trial.

### Confidentiality

2.4

The participants’ data collected during this study will be kept confidential. Study staff will have access to the data as well as the participants’ medical records as they pertain to this study. Published results will not contain any information that would identify individual participants.

## Strengths and limitations

3

To date, only oral supplementation with antioxidant agents has been proven to slow the progression of dry AMD (26). Recently, the FDA has approved new drugs, the complement inhibitors Avacincaptad Pegol and Pegcetacoplan, for the late stage of dry AMD, but they have not received the approval from the European Medicines Agency. Intervening in the progression of dry AMD by repurposing OAB therapy would be faster and more cost-effective than developing a new drug because the original drug’s safety, dosage, and toxicity profiles are already known. Whether the mirabegron dosage usually used to counteract urinary incontinence in OAB patients might be potentially effective in preventing retinal vessel proliferation is unknown. It is also unknown how long mirabegron should be administered to see any potential effect on dry AMD progression.

## Discussion

4

Previous exploratory studies in OAB patients failed to demonstrate noticeable effects of mirabegron on visual function. In fact, ocular adverse effects following bladder medication with mirabegron seem to be uncommon and rather dependent on drug dosage, with good tolerability at lower dosages (27). On the other hand, in OAB patients with healthy eyes, mirabegron was found to increase choroidal thickness as an index of its potential efficacy on choroidal vascularity (17). In addition, no significant effects of mirabegron on macular and choriocapillary parameters were recently demonstrated by Cicek et al. (16) in OAB patients without ocular pathologies.

Despite the expanding field of investigation on β3-AR-associated therapies, managing proliferative retinopathies with mirabegron would revolutionize retinal therapy. In this respect, a non-invasive treatment, that is inexpensive, well-tolerated and has few adverse effects would prove to counteract the major burden of eye diseases.

The candidacy of mirabegron as anti-angiogenic drug is based on a number of studies supporting the possibility that dry AMD may be characterized by an early phase of choriocapillaris impairment leading to chronic hypoperfusion activating, in turn, a hypoxic environment that triggers the pro-angiogenic cascade, which culminates in pathological neovascularization thus marking the transition from dry to wet AMD (28–30). In this regard, anti-VEGF treatment, by inhibiting any form of vascularization - both physiological and pathological - may perpetuate the state of retinal hypoperfusion that drives AMD progression. Conversely, treatment with mirabegron might counteract progressive hypoperfusion and therefore reduce or eliminate the need for transition toward the wet form.

In this respect, our preliminary findings in the model of oxygen-induced retinopathy suggest a major effect of β3-AR in inhibiting proangiogenic signaling and favoring endothelial cell homeostasis by activating nitric oxide bioavailability through β3-AR coupling to the nitric oxide synthase pathway (15). Considering that β3-AR activation triggers a cascade of events that, in the bladder, leads to detrusor muscle relaxation while, in the retina, plays a pèotential role in regulating neovessel proliferation in response to an ischemic insult, we hypothesized that β3-AR stimulation with mirabegron could be useful to prevent dry AMD from transitioning to wet AMD by impeding the development of leaky new blood vessels in the macula (Figure 2).

**Figure 2 fig2:**
[figure not shown]
Mirabegron efficacy in the bladder and the retina. In OAB, β3-AR coupling to Gs not only leads to the relaxation of the detrusor muscle through increased levels of cAMP but also acts presynaptically at the level of the parasympathetic nerve terminals to regulate Ach release. Ach coupling to M3-R, through Gq, leads to detrusor muscle contraction by activating PLC that in turn generates IP3 by which Ca^++^ is released by the sarcoplasmic reticulum. In AMD, potential mechanisms mediating reduced vessel proliferation limiting angiogenesis progression include β3-AR activation by NE released after hypoxia-induced overactivation of the sympathetic system. β3-AR coupling to Gi leads to increased NO production that, in turn, prevents HIF-1 dimerization by activating prolyl hydroxilases finally leading to reduced retinal vessel proliferation. AC, adenylyl cyclase; Ach, acetylcholine; AMD, age-related macular degeneration; cAMP, cyclic adenosine monophosphate; Gq, phospholipase C-stimulating G protein; Gs, adenylate cyclase-stimulating G protein; HIF-1, hypoxia-inducible factor 1; IP3, inositol trisphosphate; M3-R, muscarinic acetylcholine receptor M3; NE, norepinephrine; NO, nitric oxide; OAB, overactive bladder; PLC, phospholipase C; β3-AR, β3 adrenoceptor.

This study will provide data to determine if mirabegron, used in patients with OAB and concurrent AMD, can safely and effectively reduce the conversion of eyes from dry to wet AMD. Any favorable results of this research could open new perspectives and original scenarios to verify the role of off-label mirabegron in preventing neovascular diseases of the eye.

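### Safety is posed as a comparative question, but the only between-group safety inference is a difference test that cannot support the word *safely* at this sample size

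*Protocol article*

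**What the plan says.** Section 2.1 gives the purpose of the two-arm study as "to compare the safety and efficacy of either mirabegron (50 mg/day) or solifenacin (5 mg/day) in OAB patients". The last paragraph of section 4 (Discussion, after Figure 2) says the data will serve to determine whether mirabegron "can safely and effectively reduce the conversion of eyes from dry to wet AMD".

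The safety analysis is set out in section 2.3 and has two parts:

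- The cardiac and respiratory measures are summarised only. The plan is that they "will be reported as the number and percentage of patients with pathological values, without correlation to other variables", so no test is attached to them.
- For adverse events the article does name a between-group test, and it is the only one on safety: "Adverse event rates will be compared using χ^2^ or Fisher’s exact tests".

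The general rule in the same section is "Statistical significance will be set at a two-sided α = 0.05". The 95% confidence intervals promised there appear in the sentence on the primary adjusted analyses and are not explicitly extended to adverse events. The sample size is derived only from conversion to wet AMD: 12% against 3%, giving 134 per group net and 156 per group enrolled. The article states no expected adverse event rate.

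**The concern.** A χ² or Fisher test asks whether two rates differ. If it rejects in the direction of harm, that is evidence against the drug. If it does not reject, nothing follows about safety unless one also knows how large an excess the data rule out. The article pairs this test with a question about whether the drug works *safely*, in a study whose size was never set with safety in mind.

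At stake is how the results are read. If harms are uncommon, a non-significant comparison is the likely outcome even when the true rate is doubled. A p-value reported without an interval gives the reader no way to see that.

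**Working it through.** **1. The plan's own sample size.** Inputs from section 2.3: p₁ = 0.12, p₂ = 0.03, mean p = 0.075, two-sided α = 0.05, power 80%. The standard pooled formula is

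n = [1.960·√(2·0.075·0.925) + 0.842·√(0.12·0.88 + 0.03·0.97)]² / 0.09²
= [1.960·0.3725 + 0.842·0.3670]² / 0.0081
= (0.730 + 0.309)² / 0.0081 ≈ 133.3, rounded up to 134 per group.

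This reproduces the stated figure. It depends only on conversion rates. After 15% attrition, 156 × 0.85 = 132.6, or about 133 evaluable per group. Safety is therefore examined at 133 to 156 per group.

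**2. Chance of missing a true doubling.** The solifenacin event rate is an assumption. For each assumed rate p, with a mirabegron rate of 2p, all 2×2 tables were enumerated under independent binomials. The miss rate is 1 − P(two-sided p-value at or below 0.05).

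| Solifenacin vs mirabegron | n = 133: χ² / Fisher | n = 156: χ² / Fisher |
|---|---|---|
| 1% vs 2% | 92% / 98% | 90% / 98% |
| 2% vs 4% | 86% / 93% | 84% / 91% |
| 5% vs 10% | 66% / 75% | 62% / 69% |
| 10% vs 20% | 37% / 43% | 30% / 35% |
| 15% vs 30% | 16% / 19% | 10% / 13% |
| 20% vs 40% | 4.9% / 6.4% | 2.5% / 3.4% |

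The miss rate is thus about 30–98% for comparator rates of 1–10%, and about 3–19% for rates of 15–20%.

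**3. What an interval would show.** With equal observed rates p, the 95% half-width for the risk difference is 1.96·√(2p(1 − p)/n).

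- p = 0.05, n = 133: 1.96·√(2·0.05·0.95/133) = 0.052. With n = 156 it is 0.048.
- p = 0.01: 0.024 and 0.022.
- p = 0.10: 0.072 and 0.067.

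At a 5% rate in both arms, an excess of about 5 points, which is a doubling, would still lie at the edge of the interval.

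**4. Size needed to exclude a doubling.** With equal true rates, margin p, one-sided 0.025 and 80% power, n = 2p(1 − p)(1.960 + 0.842)²/p². This gives 1555 per group at 1%, 770 at 2%, 299 at 5%, 142 at 10% and 89 at 15%. The planned size could exclude a doubling only for events with a comparator rate of about 10% or more.

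**The case against.** Four points can be made for the plan.

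**No rule equates p > 0.05 with safety.** A reader might infer that a non-significant test will be taken as proof of safety. The documents do not say so: section 2.3 says only that rates will be compared, and the Discussion speaks tentatively of providing data. A reader might also see that logic in section 2.1, "Mirabegron displays no significant increase in major adverse cardiovascular events". That sentence describes the drug's existing profile, and the text that follows it gives expected sizes (about 1 bpm; 0.4–0.6 mmHg), not a p-value from this trial. This objection stands in full.

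**The test is not the only safety information.** Section 2.3 also plans counts and percentages of patients with pathological values. That is correct, so it would be wrong to say that the safety conclusion rests on the test alone. Those counts are stated without a between-group comparison or a bound, so they do not fill the gap.

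**Unpowered safety reporting is ordinary, and details may sit elsewhere.** A study sized on efficacy is normal practice, and margins or adverse event intervals could be in a full protocol or analysis plan that is not shown. Their absence from a condensed article is not the point here. What remains is what the article itself fixes: a comparative safety question and a named test that cannot answer it in the affirmative. Requiring a non-inferiority margin would be a design preference, and step 4 shows that this study could seldom meet one for uncommon events.

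**The miss rates depend on assumed event rates.** This also stands. The lower rates are plausible for the cardiovascular events named in section 2.1: patients with uncontrolled hypertension, tachycardia or atrial fibrillation are excluded, and participants must already have had at least 6 months of treatment. A broad category such as any adverse event could well exceed 10%, where the test performs much better.

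**Conclusion.** The point holds as a mismatch between the stated question and the stated method. The only between-group safety inference is a difference test, and a non-significant result from it could not support *safely*. On the assumption of comparator rates of 1–10%, a true doubling is missed in about 30–98% of trials at 133 to 156 per group. The figure falls to about 3–19% at 15–20%, so the higher range must not be quoted without its assumption. The calculation takes participants as independent and ignores confounding. A difference test would leave this problem even if perfectly adjusted.

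The conversion analysis is unaffected. This is an inexpensive improvement to the safety reporting and to the wording of the conclusion.

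**What to change.** In section 2.3, replace the bare comparison with an estimate: the participant-level risk difference (mirabegron minus solifenacin) with its 95% confidence interval, for any adverse event and for cardiovascular events. Keep the χ² or Fisher p-value as descriptive, and state that a non-significant result is not evidence of safety.

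In the last paragraph of section 4, change the aim to wording such as: determine whether mirabegron use is associated with less conversion, and describe adverse events.

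An upper limit for the acceptable excess, fixed before the data are seen, is optional and for the investigators to decide.

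The cost is a few sentences and one interval per safety endpoint, with no extra patients or visits. The downside is a weaker safety statement.
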